**Study duration:**

End of study is 1 year post LPFV. Therefore expected maximum study duration is 8-9 months (Period of recruiting) accrual + 12 months for follow-up.

**Primary Objective**

- To further characterize efficacy of second line ipilimumab monotherapy 3mg/kg given according to the MDX010-20 protocol in a broad range of pretreated metastatic melanoma patients seen in daily clinical practice

**Primary Endpoint**

- Overall survival rate at 12 months defined as the rate of patients alive 12 months after the date from the first study treatment for complete study population

**Secondary Objective(s)**

To explore safety and additional efficacy parameters of the ipilimumab treatment in certain subgroups: (cutaneous versus uveal versus mucosal melanoma; LDH < 2 ULN versus LDH ≥ 2 ULN; status brain metastases versus no brain metastases in medical history; b-raf mutation positive versus b-raf mutation negative; HLA-A2 positive versus HLA-A2 negative)

Secondary objectives are

- Safety / toxicity according to the CTC Criteria (Version 4.0)
- Efficacy according to immune-related response criteria (ir-RC) at any time during treatment
- Efficacy according RECIST criteria
- Progression free survival rate at 6 months
- Overall survival at 1 year in the subgroups (cutaneous, uveal, mucosal)
- To explore clinical efficacy of ipilimumab in relation to b-raf mutation status, brain metastases, LDH, HLA-A2 status

**Exploratory objectives are**

- To examine the value of peripheral blood absolute lymphocyte count (ALC) as a predictive biomarker in various patient cohorts with unresectable stage III-IV melanoma treated with ipilimumab monotherapy
- To evaluate possible surrogate markers in peripheral blood and tumour biopsy (translational research program)

**Secondary Endpoint (s)**

- All adverse events  $\geq$  Grade 3 according to CTCAE, Version 4.0 criteria, that are definitely, probably, or possibly related to the administration of the investigational agents will be assessed.
- Overall response rate (PR+CR) according to immune-related response Criteria (ir-RC) at any time in the study.
- Disease control rate irDCR (rate of CR or PR or SD) according to immune-related response Criteria (ir-RC) at any time in the study.
- Overall response rate (PR+CR) according to RECIST criteria at any time in the study.
- Disease control rate (CR or PR or SD) according to RECIST criteria at any time in the study.
- Progression free survival rate at 6 months, PFS is defined as the time from the first study treatment date until the first documented tumor progression date (as defined by immune related response criteria) or date of death, whichever occurs first.
- Overall survival
- Clinical efficacy parameter (1-year OS, ORR, DCR, PFS at 6 months) according to b-raf mutational status of tumor (b-raf V600E yes versus no), brain metastases, LDH and HLA-A2

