### **1.2 Product Development Rationale**

A large clinical phase II is proposed to treat a broad range of metastatic melanoma patients who have failed or did not tolerate at least one prior systemic treatment in metastatic or non-resectable stage III disease in order to gain more information about and further characterize efficacy and safety of ipilimumab in a broad range of clinically relevant patient cohorts seen in daily routine, neither addressed in MDX-010-20 study nor in CA184-024. Enrollment will not be restricted to any specific HLA subtype and patients with uveal or ocular melanoma can be treated with ipilimumab as well. Furthermore patients with brain metastases and documented control for at least 3 months will be eligible. Potential predictive markers (ALC, b-raf mutation

status) will be prospectively evaluated. Wide access to ipilimumab in skin cancer-specialized clinical centers will be achieved in addition to a standardized evaluation of its clinical results and currently employed algorithms so cope with occurring adverse events. Patients will be treated according the MDX-010-20 protocol with ipilimumab monotherapy 3mg/kg four times during the induction phase only. Patients who benefit from therapy (stable disease of  $\geq 3$  months beginning at Week 12 or patients with initial partial or complete response at Week 12 assessment) and did not show any immune-related adverse event (irAE)  $\geq$  grade 3 will be eligible for treatment re-induction in the case of melanoma relapse. RE-induction will be part of the study if relapse occurs during 12 months after first receipt of study medication. Re-induction will not be part of the protocol if relapse is experienced after individual end of trial (12 months post first receipt of study medication)

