## 5 STUDY THERAPY WITH IPILIMUMAB

### 5.1 Induction Treatment

Subjects enrolled after IC will receive ipilimumab according to the protocol of the completed Medarex study MDX010-20 (Hodi et al., NEJM, 2010) as a single agent at a dose of 3mg/kg for 4 times over 10 weeks (1 cycle): The day subjects receive the first dose of protocol ipilimumab therapy will define Day 1. Ipilimumab, 3 mg/kg, day 1 (W1), 22 (W4), 43 (W7), 64 (W10) must be administered intravenously over a 90-minute period every 3 weeks for a total of four doses, as tolerated. This dose demonstrated an overall survival benefit for the first time in treating metastatic melanoma in a controlled randomized clinical study (Hodi et al., NEJM, 2010).

- Electrocardiogram (ECG) examination should be performed during screening and week 12. Patients with an existing myocarditis are excluded from this study. For patients with suspicion of myocarditis e.g. dyspnoea, functional insufficiency etc. ECG examinations have to be performed before each treatment.
- Laboratory evaluations should be performed (refer to section 6.1.1.2) and the results examined before administration of each ipilimumab dose.
- As durable disease stabilization and/or objective tumor response can be seen after early progression before Week 12, it is recommended that, in the absence of dose-limiting toxicities (eg, serious irAEs), all four doses of ipilimumab be administered over the initial 12 weeks even in the setting of apparent clinical progression, providing the subject's performance status remains stable.
- All subjects who enter the induction period, including those who may have discontinued treatment for drug-related AEs should obtain a 12-week, 24-week 36-week and 48 week tumor assessment. Those patients who have evidence of clinical progression during the induction period, should obtain further tumor assessment according to Standard of Care.
- Based on clinical experience in the ongoing and completed melanoma studies, the following recommendations apply for subject management in light of the Week 12 or later tumor assessments:
  - The appearance of new lesions in subjects with other stable or shrinking baseline tumor burden may be experiencing clinical benefit and should continue in follow-up before alternative anti-cancer agents are considered. These subjects can be seen to have continued tumor shrinkage in follow-up scans.

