**6.4.3.3. Determination of Overall Response Using RECIST Criteria**

Overall Response (OR) is determined as the combination of assessments of *measurable* and *non-measurable* lesions using the following criteria:

| Measurable lesions | Non- measurable lesions | New lesions | Overall response |
|---------------------------|--------------------------------|--------------------|-------------------------|
| CR                 | CR                      | No          | CR               |
| CR                 | SD                      | No          | PR               |
| PR                 | SD                      | No          | PR               |
| SD                 | SD                      | No          | SD               |
| PD                 | any                     | Yes or No   | PD               |
| Any                | PD                      | Yes or No   | PD               |
| Any                | any                     | Yes         | PD               |

Best OR is the best confirmed response designation over the study as a whole, recorded between the date of first dose until the last tumor assessment for the individual patient in the study. The assessment of response at 12 weeks has particular emphasis due to the mechanism of action of ipilimumab inducing immune responses as basis for clinical responses. For the assessment of best OR, all available assessments per patient are considered. CR or PR determinations included in the best OR assessment must be confirmed by a second (confirmatory) evaluation meeting the criteria for response and performed no less than 4 weeks after the criteria for response are first met.

Imaging of the brain by MRT or CT, chest, abdomen and pelvis by CT scan is required at screening (ie, baseline) and at each tumor assessment visit in 12-week intervals, regardless of the location of known metastases. Similar methods of tumor assessment and similar techniques (CT or MRT) must be used to characterize each identified and reported lesion at screening and during subsequent tumor assessments. Imaging-based evaluation is preferred to clinical examination.

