#### 6.4.4.5. Immune-Related Best Overall Response Using irRC (irBOR)

irBOR is the best confirmed irRC overall response over the study as a whole, recorded between the date of first dose until the last tumor assessment before subsequent therapy (except for local palliative radiotherapy for painful bone lesions) for the individual subject in the study. For the assessment of irBOR, all available assessments per subject are considered.

irCR or irPR determinations included in the irBOR assessment must be confirmed by a second (confirmatory) evaluation meeting the criteria for response and performed no less than 4 weeks after the criteria for response are first met.

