#### 9.3.2. Secondary Efficacy Parameters

To assess safety and additional efficacy parameters of the ipilimumab treatment.

Secondary endpoints are

- Safety / toxicity according to the CTC Criteria (Version 4.0): All adverse events  $\geq$  Grade 3 according to CTCAE, Version 4.0 criteria, that are definitely, probably, or possibly related to the administration of the investigational agents will be assessed and described using descriptive statistics.
- Overall response rate - irOR (irBOR of irPR or irCR) according to immune-related response Criteria (ir-RC) (see 6.3.4.5), and OR (BOR of PR or CR) according to RECIST (see 6.3.3.3).
- Disease control rate - irDCR (irBOR of irCR or irPR or irSD) according to immune-related response Criteria (ir-RC) (see section 6.3.4.5), and DCR (BOR of PR or CR) according to RECIST (see 6.3.3.3).
- Progression free survival rate at 6 months. PFS is defined as the time from the first study treatment date until documented tumor progression (irPD) date (as defined by immune related response criteria) or date of death, whichever occurs first.

Exploratory endpoints

Pharmacodynamic effects of ipilimumab on Absolute Lymphocyte Count (ALC) and correlation of ALC to anti-tumor activity (ORR) of ipilimumab during induction phase (W12)

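### irDCR, and RECIST DCR as the synopsis defines it, credit stable disease with no minimum time from first dose, so one non-progressing scan before week 12 counts as disease control whatever follows

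*Protocol*

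**What the plan says.** The synopsis, under Secondary Endpoint(s), defines "Disease control rate irDCR (rate of CR or PR or SD) according to immune-related response Criteria (ir-RC) at any time in the study" and, for RECIST, "Disease control rate (CR or PR or SD) according to RECIST criteria at any time in the study". Section 9.3.2 builds the immune-related rate on best response, "irDCR (irBOR of irCR or irPR or irSD", but writes the RECIST rate as "DCR (BOR of PR or CR) according to RECIST", which leaves stable disease out.

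Sections 6.4.3.1 and 6.4.4.4 define SD and irSD as what remains when neither response nor progression applies. Neither gives a minimum interval from first dose. Section 6.4.4.5 says "For the assessment of irBOR, all available assessments per subject are considered", and section 6.4.3.3 says "For the assessment of best OR, all available assessments per patient are considered". Both run from the date of first dose. Both require confirmation at least 4 weeks later for complete and partial response only.

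Scheduled scans fall at weeks 12, 24, 36 and 48. Section 5.1 adds: "Those patients who have evidence of clinical progression during the induction period, should obtain further tumor assessment according to Standard of Care". Section 9.4 makes a treated patient with measurable disease response-evaluable once there is a baseline and at least one on-study tumour assessment, of any date. Section 9.5 uses that population as the denominator for irDCR and DCR.

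**The concern.** A disease control rate is normally read as the share of patients whose disease was held for some clinically relevant time. Here the time element comes only from the scan schedule and is not part of the definition. A patient scanned before week 12 whose lesions have not yet grown enough to meet progression is SD on that date, and that becomes the best response. Later progression or death does not remove it. Appendix 9 likewise takes the best response before progression.

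The effect runs one way: early scans can add patients to the numerator but cannot remove any. It also varies with local practice, because the same patient is counted as controlled at a site that scans early and is not counted at a site that waits. The irRC rate is the more exposed, since section 6.4.4.3 says new lesions alone are not progression.

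The protocol does attach time to stable disease elsewhere. Section 1.2 describes patients who benefit as having stable disease for at least three "months beginning at Week 12 or patients with initial partial or complete response at Week 12 assessment". That is a condition for re-induction and does not define this endpoint, but it shows that the disease control definition lacks any comparable condition.

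**Working it through.** The protocol states no expected DCR, no precision target for it and no frequency of early scans, so there is no figure of its own to reproduce. The check has three steps.

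**1. Does any text make week 12 a condition for SD?** The synopsis (Examinations), the Time and Events Schedule and sections 6.4.2.2, 6.4.3.1 and 6.4.3.3 place assessments at 12-week intervals. None of them, nor sections 6.4.4 to 6.4.5, 9.3.2 to 9.5 or Appendix 9, says that an earlier scan is disregarded or that SD must last a given time. The week-12 minimum therefore holds only for patients scanned on schedule.

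**2. Which progressing patients would still read as SD on an early scan?** Assume constant exponential growth to a proportional increase g at week 12. The time at which the progression threshold p is crossed is t = 12 × ln(1 + p) / ln(1 + g). The thresholds are p = 25% for irRC and 20% for the RECIST sum of diameters.

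- irRC, g = 60%: 12 × ln 1.25 / ln 1.6 = 5.7 weeks
- irRC, g = 100%: 12 × ln 1.25 / ln 2 = 3.9 weeks
- irRC, g = 200%: 12 × ln 1.25 / ln 3 = 2.4 weeks
- RECIST, g = 44%: 12 × ln 1.2 / ln 1.44 = 6.0 weeks, provided there is no new lesion

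A slower grower scanned at week 4 or 5 is SD although clearly progressing by week 12. A tumour that doubles by week 12 already reads as progression by week 4.

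**3. What does this do to the rate?** Let M be the patients with an assessment at week 12 or later, x those with disease control there, and k the patients whose only on-study assessment is an early SD scan. As written, the rate is (x + k)/(M + k). With a minimum-time rule and the same denominator it is x/(M + k). The difference is k/(M + k).

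Assumptions, none of them from the protocol: M = 160, base rate 28% (x = 0.28 × 160 = 44.8), k = 5 to 20.

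| k | As written | With minimum time | Difference |
|---|---|---|---|
| 5 | 49.8/165 = 30.2% | 44.8/165 = 27.2% | 3.0 points |
| 20 | 64.8/180 = 36.0% | 44.8/180 = 24.9% | 11.1 points |

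If the k patients also have a week-12 scan showing progression, they are already among the 160 and only the numerator moves: 0.28 + 5/160 = 31.1% and 0.28 + 20/160 = 40.5%.

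For early-scan-only patients, with M from 140 to 180 and k from 2 to 20, the difference k/(M + k) runs from 2/182 = 1.1 points to 20/160 = 12.5 points. In a uveal or mucosal cohort of the planned 20 patients, one such patient is 1/20 = 5 points.

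**The case against.** The best defence is the schedule. Measurement is set at 12-week timepoints and section 6.4.3.1 ties RECIST response to the re-staging visits, so the available assessments could be read as the scheduled ones. That would give a 12-week minimum in practice. It stands as a reason why the problem may be infrequent. It does not close the gap, because nothing excludes an off-schedule scan.

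The protocol's support for early scans in failing patients is also limited. The standard-of-care sentence in section 5.1 gives no timing, and it can be read as covering assessments after the scheduled ones. The close imaging foreseen in section 6.4.5 is for patients with tumour increase but without rapid clinical deterioration.

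A reader might infer that early scans of deteriorating patients generally score as disease control and inflate both rates. The documents do not support that. The scan must not meet progression, and step 2 shows that fast growers fail this within a few weeks. Under RECIST any new lesion is progression. RECIST DCR as written in section 9.3.2 does not count SD at all, so the point is unqualified only for irDCR.

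It is also fair that section 9.5 makes every analysis other than the primary exploratory, and that 6-month PFS, reported alongside, counts early progression and death as failures.

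**Conclusion.** The point holds for irDCR in both places where it is defined, and for RECIST DCR as the synopsis defines it. It is not something left open for the SAP: the protocol itself fixes the open time frame and the use of all assessments, so an SAP that added a minimum time would depart from it.

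The direction is certain and the size is not. The 30% to 36% range, and 31% to 41% for patients already in the denominator, illustrate assumed inputs and should not be read as estimates of this trial's bias. The base rate, the number evaluable and the number of early-scan patients all lack a source in the protocol.

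The consequence is confined to secondary, descriptive rates. No test, decision rule or sample size depends on them, and the 1-year survival rate is untouched. The change is still worth making, because it removes a one-directional dependence on site practice at almost no cost.

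**What to change.** In the synopsis and section 9.3.2, state that SD or irSD counts toward disease control only when documented at the scheduled week-12 assessment or later. Give that assessment a visit window: the Time and Events Schedule shows one for treatment visits but none for re-staging visits, and without it a scan slightly ahead of week 12 could be disqualified. State that a patient whose only non-progressing assessment is earlier stays in the denominator as no disease control. Leave the complete and partial response rules unchanged.

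In the same edit, reconcile the RECIST DCR definition in section 9.3.2 (partial or complete response only) with the synopsis (SD included).

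The cost is a sentence or two. No new data are needed beyond the scan dates that the assessments already carry. The reported disease control rate will be somewhat lower.

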**Exploratory Endpoints**

- Pharmacodynamic effects of ipilimumab on Absolute Lymphocyte Count (ALC) and correlation of ALC to anti-tumor activity (ORR) of ipilimumab during induction phase (W12)
- Evaluation of possible surrogate markers in peripheral blood and tumour biopsy (translational research program)

**Sample Size Justification**

Assuming that the entire study cohort of an estimated 200 patients will behave as pretreated cutaneous melanoma patients treated with 3 mg/kg and re-induction for eligible patients as in MDX010-20 trial where the median survival rate of 10.1. months and a 1-year-survival rate of 45.6 % (0.5) was seen, the width of the 95% CI will maximally be 14%, corresponding to a lower confidence limit of 0.43 and an upper of 0.57.

The study includes patient subgroups (uveal, mucosal, with or without asymptomatic brain metastases, with or without elevated LDH levels) for which we currently have only limited efficacy data for ipilimumab on. Retrospective studies suggest the median survival for mucosal melanoma in Stage IV is around 6 months (corresponding assuming an exponential distribution) to about 13% survival rate at 1 year), a median survival for uveal melanoma is around 11 months (corresponding

to about 25% survival rate at 1 year) and a median survival for asymptomatic brain metastases is around 5 months (corresponding to about 13% survival rate at 1 year) (Penel et al., Invest New Drugs, 2008; Becker et al., Brit J Cancer, 2002; [name] et al., Ann Oncol 2006).

Given the differing median survivals for uveal and mucosal melanoma prior to treatment with ipilimumab, the OS at 1 year will be presented separately for the cohorts, uveal, mucosal and cutaneous melanoma with or without asymptomatic brain metastases. Assuming 10% (N=20) subjects enrolled have uveal melanoma, and a further 10% have mucosal melanoma, whilst 80% (N=160) of those enrolled have cutaneous melanoma, the width of the 95%CI will, for any survival rate at 1 year, maximally span 41% for the uveal and mucosal cohorts, and 18% for the cutaneous cohort.

### Statistics

The primary endpoint is the one year survival rate.

As a simple rate, it will be calculated as the number of patients being still alive 12 months after their first administration of the study treatment divided by the number of patients having received at least one administration of the study treatment. Only subjects known to be alive at 1 year will be included in the numerator. Exact (Clopper and Pearson) two-sided 95%CI will be given.

As a time to event variable, it will be derived from the Kaplan-Meier curve based on the survival data from all subjects receiving at least one administration of the study treatment. In this case missing data will be censored at the last contact. Two-sided 95%CI will be given.

Apart from the primary endpoint descriptive statistics will be used.

Results will be presented overall and per cohort (cutaneous versus uveal versus mucosal melanoma). Results may also be presented for the subgroups:

- (1) – LDH < 2 ULN versus LDH ≥ 2 ULN
- (2) - status brain mets versus no brain mets in medical history
- (3) - b-raf mutation positive versus b-raf mutation negative
- (4) - HLA-A2 positive versus HLA-A2 negative

Proportions (Survival rate at 1 year, irOR, irDCR, irPFS at 6 mths) will be presented with exact (Clopper and Pearson) two-sided 95% CI. irOR, irDCR and irPFS are defined according to the irRC. The date of origin for the survival rate at one year and irPFS at 6 months is the date of the first ipilimumab dose. Only subjects known to be progression free at 6 months / alive at 1 year will be included in the respective numerators. Any subject receiving at least one dose of ipilimumab will be included in the denominators.

Additional analyses treating survival and PFS as time to event endpoints will be performed i.e.: Kaplan-Meier plots will be produced. Survival will be measured, regardless of any re-induction, from the date of the first ipilimumab dose given on-study until date of death. Survival time for subjects whose date of death is unknown, will be censored at the last date of contact. PFS will be measured, regardless of any re-induction, from the date of the first dose of ipilimumab until the first on-study documented date of progression as per irRC, or date of death, whichever comes first. PFS time of subjects not known to progress or die, will be censored at the date of the last tumor assessment. Median survival, median PFS, survival rate at 1 year and PFS rate at 6 months, all as derived from the Kaplan-Meier curves, will also be presented, together with two-sided 95%CI.

Safety will be reported for 70 days post last treatment. This period will be considered the on-study safety period. The analysis of safety will be based on the frequency of AEs, relationship to ipilimumab and their severity for all treated subjects (i.e.: all subjects receiving at least one dose of ipilimumab). Worst toxicity grades per subject will be tabulated for all AEs. Additionally, drug-related grade 3 or more AEs, immune-related, and serious AEs will be tabulated separately, and listings by subject will be produced for all deaths, all SAEs and all AEs leading to discontinuation of study drug.

